## Abstract

**Background:**

Multimorbidity, the presence of 2 or more chronic conditions, is becoming increasingly prevalent worldwide, resulting in significant impacts on health care systems. For people with multimorbidity, self-management is challenging, requiring engagement in several tasks. Digital health platforms have been widely acknowledged as having the potential to enhance self-management practices for those with chronic conditions. However, limited longitudinal studies have explored the effectiveness of digital health platforms that support multimorbidity self-management or issues relating to their implementation and scalability in practice.

**Objective:**

The aim of this study is to determine the effectiveness and implementation of a digital health platform, ProACT, with support services including clinical triage and a care network (consisting of informal and formal caregivers and health care professionals) compared to the use of the platform alone and compared to standard care.

**Methods:**

An effectiveness-implementation type 1 hybrid study will be conducted across 3 European countries. A total of 720 older adults aged 65 years or older with multimorbidity (2 or more of the following: diabetes, a chronic respiratory disease, chronic heart failure, and chronic heart disease) will be recruited and randomized into 1 of 3 trial arms. Those in trial arm 1 will be invited to have up to 5 care network members participate with them, resulting in a maximum of 1500 care network participants. Effectiveness will be assessed through a 3-arm pragmatic randomized controlled trial, while implementation issues will be addressed via a process evaluation. Primary outcomes for participants with multimorbidity are quality of life and health care use, while secondary outcomes focus on the potential of the ProACT platform to support multimorbidity self-management (eg, self-efficacy, usability, engagement, and symptom stabilization). Primary outcomes for informal caregivers in the care network include caring burden, while secondary outcomes for all care network members include usability, engagement, satisfaction, and overall experiences with ProACT. Additional outcomes related to the process evaluation include the reach, uptake, and fidelity of implementation of ProACT and the way organizations implement and deliver ProACT; how they differ in this regard; and the factors underpinning these differences. A range of qualitative and quantitative data will be collected and analyzed to assess these outcomes.

**Results:**

Enrollment in the trial began in September 2022, and the trial is anticipated to end by March 2026. Trial outcomes will be submitted for publication in 2026.

**Conclusions:**

The generation of evidence-based support for the routine use of the ProACT platform in applied settings would represent considerable impact. With health care services under increasing strain and traditionally designed to support those with single morbidities, it is more important than ever to develop actionable insights and resources to empower persons with multimorbidity to self-manage their complex care needs at home, with support from their caregivers.

**Trial Registration:**

ISRCTN Registry ISRCTN34134007; https://www.isrctn.com/ISRCTN34134007

**International Registered Report Identifier (IRRID):**

DERR1-10.2196/74989

## Introduction

### Background

Approximately 50 million people in the European Union, including at least 60% of those aged 65 years and older, live with multiple chronic conditions or multimorbidity [1-3], which is typically defined as the presence of 2 or more chronic conditions in the same individual [4]. The older adult population of the European Union is also increasing; the share of those aged 80 years and older is projected to increase from 5.5% to 12.7% between 2017 and 2080 [5]. Given the link between multimorbidity and increased age [6-8], combined with rising health care expenditures and budgetary constraints, health care systems face considerable challenges in sustaining services to meet the growing demands for long-term health care provision. For instance, the European Union spends approximately US $ 816 billion per annum on chronic disease management, comprising 70% to 80% of total health care costs [9], with health care costs in general projected to rise further [10]. Health care systems need to evolve, and central to this is an understanding that multimorbidity is becoming the norm rather than an exception. At present, health care systems are designed to support those with 1 rather than multiple chronic conditions; they instead need to address the management of multiple conditions, where difficulties and conflicts in care and treatment can often arise [11-14].

For people with multimorbidity, services are often repetitive, inconvenient, and burdensome (eg, due to the need to attend multiple appointments), as well as inefficient, fragmented, and potentially unsafe (eg, people with multimorbidity may receive conflicting advice from different clinicians in relation to different conditions) [15-17]. Those with multimorbidity must also often take several medications, which can be difficult to keep track of, with some combinations potentially dangerous [18,19]. There is a need to improve best practices around the provision of well-coordinated person-centered care. One way to achieve this is to empower people with multimorbidity to use digital health technology to play an active role in the self-management of their health and well-being, supported by their care networks. A digital integrated care platform, designed with the complexities of multimorbidity in mind, may facilitate self-management at home. Such a platform may also facilitate greater coordination between people with multimorbidity and their care networks in relation to their health care; while overall, it may ensure that health care systems become more sustainable, “future-proofed,” and accessible to people with multimorbidity when necessary [20].

However, while older adults are increasingly open to using digital health technology, this technology type is still in its infancy and lacks widespread adoption [21]. Furthermore, although digital health technology has demonstrated potential to advance self-management and care for those with multimorbidity [22,23], research examining its efficacy is limited. Research into digital self-management of multimorbidity has typically explored design recommendations only [24]. Our previous work represents one of the few studies to test a digital health platform (ProACT) for multimorbidity self-management and care at a proof-of-concept level among people with multimorbidity and their care networks [24,25]. The quantitative and qualitative findings revealed that the ProACT platform was engaging and useful; the qualitative findings also revealed that it facilitated perceived improvements in participants’ health and well-being, self-management, and support [24,26,27].

### Study Aim and Objectives

The overall aim of the Scaling European Citizen Driven Transferable and Transformative Digital Health (SEURO) project is to evaluate key factors to prepare organizations, localities, and regions across the European Union to scale, sustain, and transfer people-centric digital integrated health and social care solutions for multiple disease management. To achieve this, an effectiveness-implementation hybrid (EIH) trial [28] will be carried out in Ireland, Belgium, and Sweden, with ProACT, with embedded process evaluations to understand the process for successful “real-world” implementation. Effectiveness will be assessed from the user perspective via perceived quality of life (QoL) and from the service perspective via health care use (HCU); implementation will be assessed using quantitative and qualitative data (eg, assessment of organization readiness, participants’ system use data, health care organizations’ administrative data, and interview data) collected as part of a process evaluation. Effectiveness will be assessed through a 3-arm pragmatic randomized controlled trial (p-RCT) in each trial site. Those in trial arm 1 will receive a personalized version of the ProACT platform, can invite people in their care network (eg, informal and formal caregivers and health care professionals) to participate with them, and will have access to clinical triage support. Those in trial arm 2 will receive a basic, nonpersonalized ProACT CareApp with no access to the care network or clinical triage, while those in trial arm 3 will continue to receive standard care.

The objectives of this trial are (1) to evaluate the impact of the ProACT platform on people with multimorbidity’s QoL and HCU (ie, the trial primary outcomes); participants in each trial arm will be compared on these variables; (2) to evaluate the cost-effectiveness of the personalized ProACT CareApp with care network and triage support in comparison to the nonpersonalized ProACT CareApp and control group; (3) to explore via a mixed methods approach (analysis of system and questionnaire data and interviews with participants) the potential impact of ProACT on multimorbidity self-management; (4) to evaluate the impact of the ProACT platform on informal caregivers’ caring burden; and (5) to evaluate participants’ (people with multimorbidity and care networks) overall experiences with the ProACT platform in the management of multimorbidity. Data collected from participants in trial arms 1 and 2 will also be compared. Furthermore, to explore the impact of contextual factors (eg, participants’ conditions, age, and socioeconomic status and care network participants’ motivation to take part in the trial) on fidelity of use and use outcomes (eg, reach, uptake, and acceptability); (6) to understand how ProACT is implemented and delivered in health care settings and to identify systematic differences and variation in delivery; (7) to evaluate via the process evaluation organizational readiness to transfer and optimize a digital health solution as part of the care delivery; and (8) to evaluate whether trial outcomes can inform future analysis of the impact of digital solution implementation in practice. This protocol adheres to the SPIRIT (Standard Protocol Items: Recommendations for Interventional Trials) guidelines for clinical trial reporting (Multimedia Appendix 1) [29].

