**Trial arm 3**
Usual care (no technology)

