### Sample

Three main participant groups will be recruited for the EIH trial in each of Ireland, Belgium, and Sweden: older people with multimorbidity, care network members, and partner organization management and staff involved in overseeing and implementing ProACT delivery. A maximum of 1920 participants (ie, people with multimorbidity and care network members) will be recruited across the 3 trial sites. This sample will consist of a maximum of 720 participants with multimorbidity (240 at each site) and a maximum of 1200 key individuals within the trial arm 1 participants’ care networks (400 at each site). Up to 15 partner organization managers or staff (5 at each site) will also be recruited.

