### Participant Inclusion and Exclusion Criteria

Participants with multimorbidity must be aged 65 years or older, possess sufficient cognitive capacity to provide written informed consent, and have at least 2 of the following conditions: diabetes, chronic respiratory disease (eg, chronic obstructive pulmonary disease and chronic asthma), chronic heart failure, chronic heart disease (eg, coronary artery disease and cardiovascular disease, including hypertension, atherosclerosis, angina, or arrhythmia).

For care network participants to be included, the person with multimorbidity must provide consent for their participation. Care network participants must be aged 18-90 years; be providing support to a consented participant with multimorbidity in trial arm 1 (if they are an informal caregiver, they must be providing support to a participant with multimorbidity for at least 6 months; and if they are a formal caregiver, formal care quality assistant, or health care professional, they must be formally recognized as such and possess at least 2 years of experience of professionally working in a relevant health or primary care setting with people with multimorbidity with the same health conditions as those involved in this trial); have access to a tablet, smartphone, or computer with an internet connection; possess the skills to use an internet-based app or website; and possess sufficient cognitive capacity to provide written informed consent.

Partner organization management and staff must be aged 18 years or older; be overseeing and implementing the delivery of ProACT to their clients with multimorbidity; have access to a tablet, smartphone, or computer with an internet connection; and possess the skills to use an internet-based app or website.

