#### Care Network Participants

Care network participants will be asked to complete questionnaires in the same manner as participants with multimorbidity (ie, online or over the phone, with data captured through REDCap [49,50]). At the beginning of their trial periods, all care network participants will be asked to complete a questionnaire that captures their demographic information; informal caregivers will also be asked to complete the Zarit Burden Interview [51]. At the conclusion of their trial periods, all care network participants will again be asked to complete 2 questions that capture their opinion on how the use of ProACT influenced their care and any burden they may have experienced while using ProACT (ie, measured via the User Burden Scale) [47]. Informal caregivers will also be asked to complete the Zarit Burden Interview [51]; while any formal caregivers, formal care quality assistants (ie, managers of formal caregivers), or health care professionals taking part in the process evaluation may have an additional questionnaire to complete (ie, the ProTransfer questionnaire; see Process Evaluation Methodology section). All questionnaires can be completed online or over the phone, depending upon the participants’ preferences. The full list of key assessment domains and measures is available to view in Table S3 in Multimedia Appendix 2.

At the conclusion of their trial periods, the research teams will also conduct semistructured interviews or focus groups with up to 60 participants in each care network group (ie, with up to 20 participants in each care network group in each country) to collect data on their satisfaction with and attitudes toward the technology, etc. These will likely take place over the phone or online due to trial resource limitations and the anticipated wide geographic spread of care network participants within each country, particularly of informal caregivers. For health care professionals and formal caregivers or formal care quality assistants, these will take place either by phone, online, or at their place of work, depending upon what is most convenient for them. The interviews or focus groups will be audio-recorded and transcribed, and the researchers will subsequently annotate and analyze the collected data.

Finally, care network participants’ system use statistics (eg, data that capture their use of the ProACT CareApp) will be collected continuously throughout their 6-month trial period.

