The primary outcomes for informal caregivers include caregiver burden. Other outcomes for all care network participants include the usability, accessibility, and acceptability of, and engagement, satisfaction, and overall experiences with, ProACT.

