Indirect costs of the care network (informal care) will be calculated using data collected from the participants with multimorbidity and their informal caregivers. First, participants with multimorbidity will provide data on time spent on care by their informal caregivers. With the use of the opportunity costs method, this time will be converted into monetary value. Next, data collected from the informal caregivers, via the Zarit Burden Interview, will facilitate an assessment of the health gains of the time spent in care, considering the ProACT intervention. Indirect costs will be considered as an aggregated cost in this study.

The cost-utility analysis technique will underpin the quality-adjusted life years calculation. The quality-adjusted life years is a general measure used in economic evaluation that permits the valuation and comparison of the health gains of an intervention. For this calculation, the health-related QoL measurement instrument (EQ-E5-5L) will capture the self-perceived health status of the participant in a 5-digit code. Next, the code will be converted into a utility value (or utility weight), based on the country-specific value set. The result consists of the multiplication of the utility value with the period lived with the self-perceived condition.

For the secondary outcomes, such as the impact of ProACT on self-management, we may use structural equation modeling to determine the relevance and importance of different variables measured during the trial. Hitherto, there is no consensus on how to measure improved self-management. For this study, we may consider the concept of self-management as a composite measurement of different variables proven to be associated with the ability to self-manage chronic illnesses. Variables that are associated with improved self-management include, for instance, self-efficacy, health literacy, and disease knowledge, and therefore may be treated as latent variables. Using a structural equation model, such as confirmatory factor analysis, we will be able to identify the existence of a relationship between these variables and an overarching concept of self-management.

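### Caregiver burden is measured only in arm 1, so the objective of evaluating ProACT's impact on it has no comparator and can yield only an uncontrolled before-after change

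*Protocol article*

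**What the plan says.** In Study Aim and Objectives, objective 4 is to "evaluate the impact of the ProACT platform on informal caregivers" with respect to caring burden. Under Care Network Participants the article states: "The primary outcomes for informal caregivers include caregiver burden". The Abstract says the same.

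Participant Inclusion and Exclusion Criteria requires a care network member to "be providing support to a consented participant with multimorbidity in trial arm 1". The Sample section gives "a maximum of 1200 key individuals within the trial arm 1 participants" as the source of the whole care network sample. Arm 2 receives a "nonpersonalized ProACT CareApp with no access to the care network or clinical triage", and arm 3 is usual care. Under Recruitment Procedures, arm 1 participants nominate the members, who must then consent. The Overview of the p-RCT Methodology allows an arm 1 participant to take part with no care network member at all.

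On measurement, the Care Network Participants section says that at the start "informal caregivers will also be asked to complete the Zarit Burden Interview", and that they repeat it at the end. In the Data Analysis Plan, "data collected from the informal caregivers, via the Zarit Burden Interview, will facilitate an assessment of the health gains of the time spent in care". Objective 2 defines the economic contrast as arm 1 against arm 2 and the control group.

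**The concern.** Evaluating impact is a causal aim. Objective 3, by contrast, only sets out to explore a potential impact, so objective 4 reads as an effect claim. An effect needs an answer to what burden would have done without ProACT, and nobody supplies that answer, because caregivers of arm 2 and arm 3 participants are neither enrolled nor measured.

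At stake is what the trial may report. Burden may move over six months as the participant's illness moves. Scores that were high at entry tend to fall back. The caregivers who are nominated, agree and stay to the end are not a random sample of caregivers. Each of these would be credited to ProACT if the change were reported as an impact. The Limitations section does not mention the missing comparator.

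A second, conditional worry concerns the economic evaluation. A Zarit-based health gain can be computed for arm 1 only, so using it in a comparison of arms would treat the arms unequally.

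**Working it through.** **The plan's own figures.** None applies. The Sample Size Justification covers participants with multimorbidity only and gives no size, effect or test for caregiver burden. The point rests on the design.

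**Who has a Zarit score**

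| Arm | Care network enrolled | Zarit at start and end |
|---|---|---|
| 1 | Yes, up to 5 per participant, optional | Yes, informal caregivers |
| 2 | No | No |
| 3 | No | No |

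The care network maximum of 1200 equals 240 × 5, that is, all arm 1 participants times five members. Nothing is left over for the other arms.

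**What can be estimated.** Write mean burden as a + b·time + d·(time × ProACT), where b is the change that would occur anyway and d is the ProACT effect.

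- Arm 1 only: the start mean is a and the end mean is a + b + d. There are two means and three unknowns. The design matrix has rank 2 for 3 parameters, and only the sum b + d is estimable.
- Arm 1 plus a comparator measured at both times: the comparator adds the means a and a + b. The rank is 3, and d is estimable.

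The within-arm-1 change b + d is therefore available, but d alone is not.

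**How little drift is needed (illustration).** None of these inputs is in the article: 150 informal caregivers with both scores, start-to-end correlation r of 0.5 or 0.7, background drift of 0, 0.1 or 0.2 SD, no ProACT effect (d = 0), and a two-sided paired test at 0.05.

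SE of the mean change, in SD units = √(2(1 − r)/150):
- r = 0.5: √(1/150) = 0.0816
- r = 0.7: √(0.6/150) = 0.0632

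Probability of a significant result = 1 − Φ(1.96 − drift/SE) + Φ(−1.96 − drift/SE):

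| Drift | r = 0.5 | r = 0.7 |
|---|---|---|
| 0 | 0.05 | 0.05 |
| 0.1 SD | 0.232 | 0.353 |
| 0.2 SD | 0.688 | 0.885 |

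With 168 pairs in place of 150, the figures for 0.1 SD are 0.254 and 0.387, and those for 0.2 SD are 0.736 and 0.917. The calculation treats the pairs as independent. Where informal caregivers share a participant and the analysis allows for it, the effective number is smaller and the rates with drift are somewhat lower.

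**The economic link.** The Data Analysis Plan takes QALYs from the participant's own health-status instrument and bases monetary value on health care use data. Time spent by informal caregivers is reported by the participant and costed separately. The Zarit sentence describes an assessment of health gains but not where that assessment goes. Since only arm 1 has scores, any use between arms would lack values for arms 2 and 3.

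**The case against.** The strongest reply is that burden is not a trial primary outcome. Objective 1 reserves that term for quality of life and health care use and announces a comparison of arms only there. The Data Analysis Plan lists quality of life, health care use and cost-effectiveness as the primary analyses, and burden is not among them. Trial Procedures describes the aim of care network use as exploring experience and perceived usefulness. Caregivers also give a direct opinion on how ProACT influenced their care, complete the User Burden Scale, and may be interviewed. All of this stands. It means that the randomised comparison of the trial primary outcomes is untouched, and that the Zarit change is not the only caregiver evidence. It does not supply a comparator for objective 4.

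The reply also notes that the article plans no paired test and that the percentages rest on assumed inputs. That stands too. They show how sensitive an uncontrolled change is and do not measure an error in this trial. With no drift the rate is 5%.

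A reader might infer that nothing about burden can be estimated. That goes too far, because the within-arm-1 change can be. A reader might also infer that the cost-effectiveness result is biased. The article does not support that as a fact, since it never says that Zarit-based gains enter the comparison of arms.

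An appeal to a fuller analysis plan does not help on the main point. Eligibility and data collection fix the restriction, and no analysis can recover caregivers who were never measured.

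**Conclusion.** The point holds as a mismatch between claim and design. Objective 4 and the primary caregiver outcome are worded as an effect, while the data allow only an uncontrolled change in one arm, among caregivers who were nominated and agreed. This follows from the article's own eligibility, sampling and measurement rules and needs no assumption.

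The size of any misattribution is unknown. Under the assumed inputs above, drift of 0.1 to 0.2 SD alone would make a paired test significant in about 23% to 89% of trials.

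The economic part is conditional: Zarit-based gains would make the comparison of arms unequal only if they were entered in it, and the article is silent on that. The conclusions on quality of life and health care use are not affected.

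**What to change.** The Results section reports that the trial is complete in Ireland and Belgium and that recruitment in Sweden has closed, so a comparator can no longer be added in practice. The claim can still be corrected before reporting:

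1. Restate objective 4 and the caregiver outcome as a descriptive change in Zarit score within arm 1: mean change with 95% CI, allowing for informal caregivers who share a participant.
2. Drop the impact wording and the primary effectiveness label for burden.
3. Add to Limitations that burden has no comparator and that caregivers were nominated and self-selected.
4. State that Zarit data do not enter the between-arm cost-effectiveness result.
5. If participant-reported informal-care time was collected in all arms, which the article does not establish, it may be compared by arm. It should be labelled as care time, not burden.

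The cost is rewording and one descriptive analysis of data already planned. The downside is that a causal claim about caregiver burden is given up.
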